Table 1: Estimates of power to detect a range of possible relative risks, under a range of assumptions about the number of likely lansoprazole exposed TB cases

For most of the assumptions tested, we will have adequate power to detect an association with lansoprazole assuming a protective association of 0.8 or greater, which we believe would represent a clinically relevant effect size.

1. **Data Linkage Required (if applicable)**

Patient-level index of multiple deprivation data are required to assess for confounding as it is likely that risk of TB will vary by socioeconomic status. Since this is only available for patients in the linkage scheme, we propose to use practice-level index of multiple deprivation for the remainder of patients (rescaled to be on the same scale as the patient level scores, using observations where both are available). We have used this strategy successfully in previous CPRD studies.

We will also use HES (in- and out-patient data) to identify cases of TB recorded in hospital.

1. **Study Population**

The source population for this study is all patients aged 16 years or over with acceptable user status registered in the entire CPRD, with up-to-standard (uts) follow up of at least 12 months.

From the source population we will select all patients who are:

1. New users of lansoprazole; defined as people starting treatment with lansoprazole after at least 12 months uts follow up, with no previous record of receiving a PPI.
2. New users of omeprazole or pantoprazole; defined as people starting treatment with omeprazole or pantoprazole after at least 12 months uts follow up, with no previous record of receiving a PPI.

Exposure to lansoprazole, omeprazole and pantoprazole will be defined by prescription records, as conducted previously by this research group2.

All patients with a record of TB disease prior to their first PPI will be excluded from the study.

1. **Selection of comparison group(s) or controls**

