CPRD linked Hospital Episodes Statistics (HES) in- and out-patient data will also be searched for codes indicating tuberculosis (A15-A19). A sensitivity analysis restricted to the CPRD HES-linked practices and time periods will be conducted, taking the earliest of CPRD or HES identified TB disease.

Covariates to be explored for their potential confounding nature will be age, sex, calendar year, smoking behaviour, body mass index, alcohol use, ethnicity, drug abuse, the use of inhaled/oral corticosteroids, travel vaccines, antimalarials, diabetes, rheumatoid arthritis, irritable bowel disease, chronic obstructive pulmonary disease, asthma, chronic kidney disease, depression, leukaemia, lymphoma, myeloma any record signifying the use of chemotherapy, a record of HIV infection and index of multiple deprivation score. Of note, ciclosporin and tacrolimus, both immunosuppressive drugs, are known to interact with omeprazole but not other PPIs. It is possible that people at higher risk of TB will therefore be given PPIs other than omeprazole and for this reason, patients with a history of use of either drug will be excluded from the study population.

1. **Data/ Statistical analysis**

Each participant’s follow up time will begin at the first prescription for lansoprazole or omeprazole/pantoprazole. All subsequent time will be classified as one of the following

- *Lansoprazole exposed* – all time covered by lansoprazole prescriptions, including a 60 day period after the estimated end of treatment date, to allow for stock piling and non-adherence
- *Omeprazole/pantoprazole exposed* – all time covered by omeprazole/pantoprazole prescriptions including a 60 day period after the estimated end of treatment date, to allow for stock piling and non-adherence. This will be the baseline against which other exposures are compared.
- *Unexposed* – all time between lansoprazole/omeprazole/pantoprazole exposure periods, or between the end of PPI exposure and the end of follow up. This time is being handled separately as it is plausible that a period of time off a PPI may be a marker of important changes in underlying health, with an associated change in the risk of TB disease

Where patients switch directly between one PPI and another, exposure will be updated to the new PPI from the date it is prescribed, assuming stock-piled drug is no longer taken.

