End of follow up will be defined as the earliest of first recorded TB disease, death, transfer away, end of UTS or last data collection date.

Examples of how patient follow up time will be allocated are shown in Figure 1.

*Figure 1: Example Patient Exposure Timelines*

1. Lansoprazole exposure only

12 months follow up with no PPI

End uts

Lansoprazole prescription

EXPOSURE GROUP

Lanoprazole

1. Omeprazole or pantoprazole only

12 months follow up with no PPI

End uts

Omeprazole prescription

EXPOSURE GROUP

Omeprazole

or pantoprazole

1. Lansoprazole and omeprazole/pantoprazole

12 months follow up with no PPI

End uts

Lansoprazole prescription

Omeprazole prescription

EXPOSURE GROUP

Lansoprazole

Omeprazole

or pantoprazole

4. Lansoprazole with Breaks

12 months follow up with no PPI

End uts

Lansoprazole prescription

EXPOSURE GROUP

Lansoprazole

Unexposed

5. Lansoprazole, omeprazole/pantoprazole and breaks

12 months follow up with no lansoprazole

End uts

Pantoprazole prescription

Lansoprazole prescription

EXPOSURE GROUP

Lansoprazole

Unexposed

Omeprazole

or pantoprazole

The primary comparison of interest is the risk of TB comparing lansoprazole exposed time with omeprazole or pantoprazole exposed time. People starting treatment with omeprazole or pantoprazole but later receiving lansoprazole will transition to the lansoprazole group at that time and vice versa. Follow up for each patient will end at the earliest of; TB disease, transfer out, death or end of uts follow up.

Descriptive analyses will be performed, comparing the distribution of the following variables between patients starting lansoprazole and those starting omeprazole/pantoprazole: Age, sex, calendar year, smoking behaviour, body mass index, alcohol use, ethnicity, drug abuse, the use of corticosteroids, any record signifying any prior use of chemotherapy, travel vaccines, antimalarials, diabetes , rheumatoid arthritis, irritable bowel disease, chronic obstructive pulmonary disease, asthma, chronic kidney disease, depression, leukaemia, lymphoma, myeloma, a record of HIV infection and index of multiple deprivation score.

Cox regression will be used to estimate hazard ratios and 95% confidence intervals, comparing lansoprazole exposed time against omeprazole or pantoprazole exposed time. A crude model will be constructed with just the main exposure variable, followed by a model adjusting for potential confounders.

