We will fit an interaction term to look for effect modification between lansoprazole exposure and age.

As a sensitivity analysis we will vary the time following the end of estimated treatment duration after which therapy cessation is assumed, from 60 to 90 days. A further sensitivity analysis will censor all patients after a cessation or switch of PPI therapy, (cessation defined as longer than 60 days not covered by a prescription.)

1. **Plan for addressing confounding**

Potentially confounding variables have been selected based on their possible association with the risk of TB, as listed in part K. These variables will be explored and potentially adjusted for in a multivariable Cox regression model. However, we believe substantial confounding is unlikely in this study as risk factors for TB are not expected to be associated with the choice of specific PPI, with the exception of calendar year. It is possible that rates of TB have changed over time and local prescribing guidance for preferred PPI has varied over the years mainly based on cost considerations. PPI preference could also be dictated by differential drug interactions between individual PPIs, as noted above for tacrolimus and ciclosporin and people with a history of taking either drug will be excluded.

1. **Plan for addressing missing data**

There is known missingness in the smoking and alcohol status and BMI variables. From previous experience of studies involving people taking long term medication such as PPIs it is expected that <10% of patients will have missing data. We plan to conduct a complete case analysis, which relies on the assumption that the probability of these data being missing is independent of TB risk, conditional on covariates5; given the small amount of missing data, any violation of the assumption is unlikely to importantly affect the results. Ethnicity is likely to have substantially more missing data. Again, we will conduct a complete case analysis with this variable included in the model, recognising the reduction in sample size will be greater and that this is a limitation of the study.

1. **Limitations of the study design, data sources and analytical methods**

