It is possible that TB may go unidentified in some patients and therefore unrecorded in CPRD. Assuming this is non-differential between PPIs, this will only lead to a loss of power, rather than a biased estimate; however the power calculations we present are based on identified cases and so this is not expected to be a major limitation.

The timing of TB disease recorded in CPRD will not be the same as the date when infection actually occurred as we are detecting recorded diagnoses rather than actual time of infection. We are dealing with this by moving the date of TB disease to an earlier time and have planned sensitivity analyses varying the length of this time shift. However, PPI exposure tends to be for long periods in many patients and so it is not expected that timing inaccuracy for infection will have a substantial impact on the estimated exposure status of cases.

The recording of risk factors for TB is unlikely to be perfect. For example HIV status, drug abuse and exposure to chemotherapy may not be well recorded in primary care. However, we anticipate little confounding in this study, except by calendar time and possibly age, both of which are well recorded. Other possible sources of confounding we will be unable to address include clinical commissioning group, previous imprisonment and homelessness.

We anticipate that our estimate of PPI exposure times will be flawed to some extent due to lack of adherence. This will tend to lead to an underestimate of the effect size of any true association with lansoprazole, assuming the degree of exposure misclassification is non-differential in those people with and without subsequent TB disease.

As noted above, ethnicity will not be recorded for all patients and so the complete cases analysis including this variable may give a biased result. However, although ethnicity is a strong risk factor for TB, it is unlikely to be a strong deciding factor for specific PPI selection.

1. **Patient or user group involvement (if applicable)**

At this stage we do not plan to involve patients in the study; but depending on our findings it is possible we would seek patient engagement to help shape future research plans.

1. **Plans for disseminating and communicating study results, including the presence or absence of any restrictions on the extent and timing of publication**

All results will be presented at scientific conferences and published in a peer reviewed journal.

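### Confounding by clinical commissioning group is declared unaddressable, although the plan must know each patient's practice, and a practice-stratified Cox model would partly address it

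*Protocol*

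**What the plan says.** All places are in the Protocol.

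- *Limitations of the study design, data sources and analytical methods*: "Other possible sources of confounding we will be unable to address include clinical commissioning group, previous imprisonment and homelessness". On ethnicity, which the same section calls a strong TB risk factor, it says that "it is unlikely to be a strong deciding factor for specific PPI selection".
- *Plan for addressing confounding*: "local prescribing guidance for preferred PPI has varied over the years mainly based on cost considerations". TB risk factors are otherwise expected to be unrelated to the choice of PPI, calendar year excepted.
- *Data Linkage Required*: "it is likely that risk of TB will vary by socioeconomic status". Patient-level deprivation is requested where linkage exists; elsewhere "we propose to use practice-level index of multiple deprivation for the remainder of patients".
- *Exposures, Outcomes and Covariates*: "A sensitivity analysis restricted to the CPRD HES-linked practices and time periods will be conducted". The covariate list ends with "a record of HIV infection and index of multiple deprivation score"; deprivation is its only area-related item.
- *Data/Statistical analysis*: "A crude model will be constructed with just the main exposure variable, followed by a model adjusting for potential confounders". No stratum or term for practice, region or commissioning group is given.

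**The concern.** If local guidance sets the preferred PPI, the drug a patient receives depends partly on where the patient is registered. If TB rates also differ by place, for reasons that the measured covariates capture incompletely, place confounds the comparison. The argument about ethnicity does not dispose of this. A prescriber need not consider ethnicity for it to be associated with the drug; it is enough that both differ between localities.

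At stake is the interpretation of the main result. The first amendment reports that a protective association was found, so confounding by place is a live alternative explanation. The added control outcomes, myocardial infarction and herpes zoster, would reveal it only if they shared TB's geographic pattern, and the Protocol does not argue that they do.

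**Working it through.** **1. Is practice known?** Giving a practice-level deprivation score to each unlinked patient requires knowing that patient's practice. So does restricting an analysis to HES-linked practices. Follow-up ends at transfer out, so a patient's follow-up stays within one practice. The words *practice identifier* do not appear; this is an inference, but those two steps depend on it.

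**2. Does practice help without a commissioning-group code?** In a Cox model with practice as stratum, each TB case is compared only with patients at risk in the same practice. Anything constant within the practice cancels. This covers commissioning group if a practice belongs to one group, which is an assumption because the Protocol does not say so. Guidance that changes over time within a practice does not cancel, so calendar period must also be in the model.

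**3. How large could the bias be?** The Protocol gives no area data, so every area input here is assumed.

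- From the feasibility count: lansoprazole share s = 744,144 / (744,144 + 1,182,888) = 744,144 / 1,927,032 = 0.386.
- Assumed: a fraction f = 0.20 of patients in high-TB areas, TB rate R = 4 times that elsewhere, lansoprazole share d lower there, and no drug effect.
- Lansoprazole share in high-TB areas: s_h = s − d(1 − f).
- Fraction in high-TB areas: p1 = f·s_h / s among lansoprazole users; p0 = f(1 − s_h) / (1 − s) among comparators.
- Crude RR = [1 + p1(R − 1)] / [1 + p0(R − 1)].

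| d | s_h | p1 | p0 | Crude RR |
|---|---|---|---|---|
| 10 points | 0.306 | 0.159 | 0.226 | 1.476 / 1.678 = 0.88 |
| 20 points | 0.226 | 0.117 | 0.252 | 1.351 / 1.756 = 0.77 |

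Over f = 10–30%, R = 3–6 and d = 5–20 points, the crude RR runs from 0.97 to 0.69. If high-TB areas favour lansoprazole instead, the bias reverses: with f = 0.20 and R = 4, a gap of 10 points gives s_h = 0.466 and 1.724 / 1.522 = 1.13, and a gap of 20 points gives s_h = 0.546 and 1.849 / 1.444 = 1.28.

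**4. Does comparing within practice remove it?** A simulation under a true null assumed 600 practices, about 1,300 TB cases, a standard deviation of 0.5 to 1.5 for the logit of practice lansoprazole share, and 0.5 to 0.8 for the log TB rate.

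- Correlation −0.3 to −0.5 between the two: crude RR 0.65 to 0.93; practice-stratified (Mantel-Haenszel) RR 1.00 to 1.01.
- Correlation 0: both about 1.00.
- Ratio of crude to stratified variance of the log RR: 0.80 to 1.11.

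**5. What does it cost in power?** The Protocol's Table 1 at RR 0.8 was reproduced first, using power = Φ(√(D/4)·|ln RR| − 1.96), with D = 2 × exposed cases and two-sided 5% assumed. The second row multiplies D by 0.8, the low end of the variance ratios in step 4.

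| Exposed cases | 1,200 | 800 | 500 | 200 |
|---|---|---|---|---|
| Table 1 | >0.99 | >0.99 | 0.94 | 0.61 |
| Recomputed | 0.9998 | 0.994 | 0.942 | 0.607 |
| 80% of information kept | 0.998 | 0.979 | 0.884 | 0.514 |

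**The case against.** The strongest reply is that the plan already handles much of this. Deprivation and ethnicity are both listed covariates, and the practice-level fallback score itself carries area information. The figures in the working are crude ratios, whereas the reported result will include an adjusted model. This stands: only residual geographic confounding is in question. The adjustment is incomplete, however. A deprivation score does not measure local prescribing policy, and ethnicity enters only through a complete-case analysis that the Protocol itself says may be biased.

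Second, the limitation names commissioning group, not practice, and nothing shows that the team holds a commissioning-group code or practice locations. That also stands, so a reader should not infer that the statement is simply false. Practice serves as a stand-in that makes the confounder partly addressable.

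Third, the remark about local guidance is offered to explain confounding by calendar year, and does not say that high-TB areas favour either drug. That is true, and it is why no direction can be claimed.

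Fourth, the first amendment shows that the main result is already known. Replacing the primary model now would be a change made after seeing the result. This tells against replacement, but not against an added analysis.

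Finally, stratification is often left to an analysis plan, and none is shown here. The point does not rest on that omission, but on the Protocol's positive statement that this confounder cannot be addressed.

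**Conclusion.** The concern holds in a limited form. The Protocol treats as unaddressable a confounder that it could partly address with data it must already use, and its own text gives reasons to expect both drug choice and TB risk to vary by place.

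The size is unknown. The illustrative 0.88 to 0.77 spans the 0.8 that the Protocol calls clinically relevant, but it rests wholly on assumed area inputs and on a crude comparison. Adjustment for deprivation and ethnicity would be expected to shrink it, so it is nearer an upper bound for the adjusted model in that scenario. The simulated crude ratios carry the same caveat.

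A reader might infer that the reported protective association is a geographic artefact. The documents do not support that: they give no TB rates or drug shares by area, the bias could run either way, and it is nil if the two are uncorrelated across practices. Equally, null results for myocardial infarction or zoster would not exclude it. This is an inexpensive improvement, not a demonstrated flaw in the primary estimate.

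**What to change.** 1. Add, by amendment and specified before it is run, a sensitivity analysis using a Cox model stratified by general practice, with calendar period also in the model and the same covariates as the planned adjusted model. If practice strata are too sparse and region is held, use region-by-period strata.
2. Report it beside the planned adjusted model, leave the primary model unchanged, and state that it was added after the main result was known.
3. Reword the limitation: list commissioning group as partly addressable through practice, and keep imprisonment and homelessness as unmeasured. Practice strata would remove only differences in these between practices.

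The cost is one further model on data already in use. Practices with no TB case, or with only one drug group, add no information, so the confidence interval may widen. The Protocol does not give the number of practices, so the loss cannot be fixed in advance; with 80% of the information kept, power at RR 0.8 stays above 0.85 for 500 or more exposed cases but is about one half for 200.

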All new users of omeprazole and pantoprazole are to be included as the comparator group, as described in Section I above. Users of a PPI are likely to be more sick than people not using PPIs, and therefore may be at an increased risk of outcomes such as acquiring an infection. Omeparazole and pantoprazole exposed people are therefore the ideal comparator group as we assume that the choice of specific PPI is less likely to be related to underlying health, and both were found to have no effect on TB in the study that motivated this work. Other PPIs were not investigated by Rybniker et al and so have not been included here. We believe it is very unlikely that PPI choice is related to the future risk of TB.

1. **Exposures, Outcomes and Covariates**

For PPI exposure, we will use recorded information on intended treatment duration and dosage instructions to estimate likely exposure duration. Where duration is missing, we will impute the population median exposure length. From past experience of PPI prescribing in CPRD, the majority of prescriptions last 30 days.

For the outcome, we will select all clinical records indicating TB as identified using codes in Appendix 1. Our primary outcome will be defined as all codes indicating TB disease. The earliest recorded date of a code indicating the outcome will be taken as the date of TB disease. A previous study using a similar approach for TB case identification in CPRD found incidence rates comparable to Public Health England figures, suggesting reliable case ascertainment3. However, the time between TB infection and diagnosis with TB disease is known to involve a median delay of 1.26 years, but with substantial variability4 and so the aetiologically relevant exposure for a protective effect to be seen is likely to be some time earlier than the recorded diagnosis. For this reason, all TB dates will be moved earlier by 12 months in the primary analysis. As sensitivity analyses, TB dates will be defined as 1) as recorded in CPRD, 2) 2 years earlier than recorded and 3) 5 years earlier than recorded. In all analyses where the TB date is moved earlier, follow up time for both TB cases and non-cases will be censored the same amount of time earlier.

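### The claim that adherence error biases the lansoprazole effect towards underestimation needs a second condition: similar off-drug share in both drug groups, or no difference in off-PPI TB risk

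*Protocol*

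**What the plan says.** The protocol's section on limitations of the study design, data sources and analytical methods names the source of error: "We anticipate that our estimate of PPI exposure times will be flawed to some extent due to lack of adherence". It then gives the expected direction, "This will tend to lead to an underestimate of the effect size of any true association with lansoprazole", and attaches one condition, "assuming the degree of exposure misclassification is non-differential in those people with and without subsequent TB disease". It does not mention similarity of the error between the two drug groups. The same section does invoke similarity between PPIs when it discusses unrecorded TB, but the exposure paragraph does not.

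The Data/ Statistical analysis section defines three states: lansoprazole exposed, omeprazole/pantoprazole exposed and unexposed. Of the omeprazole/pantoprazole state it says "This will be the baseline against which other exposures are compared". Unexposed time is kept apart because "it is plausible that a period of time off a PPI may be a marker of important changes in underlying health", with a change in TB risk attached. Each drug state is extended by the same rule, "including a 60 day period after the estimated end of treatment date, to allow for stock piling and non-adherence". Under Exposures, Outcomes and Covariates, one rule covers gaps in the duration data: "Where duration is missing, we will impute the population median exposure length".

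**The concern.** The familiar result, that exposure error unrelated to outcome pulls the estimate towards the null, belongs to a comparison of exposed with unexposed. Here two drugs are compared, and the error the protocol names puts truly off-drug time into both drug categories. If off-drug time carries a different TB rate, each category's observed rate is pulled towards the off-drug rate by an amount that depends on its own off-drug share. If the shares differ, the ratio shifts even though the error has nothing to do with TB.

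What is at stake is how a result may be read. The first Amendment reports that a protective association has been found. The limitations sentence, as worded, invites the reader to take any such estimate as conservative, and the design does not support that without the second condition.

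**Working it through.** **The plan's own figure.** There is none to reproduce: the protocol gives no size for misclassification bias, no off-drug shares and no off-PPI TB rate. All values of a, b and r below are assumptions.

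**Set-up.** Let θ be the true HR of lansoprazole against omeprazole/pantoprazole, and r the off-PPI TB rate divided by the on-drug omeprazole/pantoprazole rate. Let a and b be the off-drug shares of time classified as lansoprazole and as omeprazole/pantoprazole. The error is unrelated to TB given true exposure, so the protocol's stated condition is met. Then

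observed HR = [(1 − a)θ + a·r] / [(1 − b) + b·r].

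**Null drug (θ = 1).** This simplifies to observed HR − 1 = (a − b)(r − 1) / [1 + b(r − 1)]. The HR is 1 only if a = b or r = 1. Otherwise its direction depends on the signs of (a − b) and (r − 1).

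**Numbers.** For a = 0.40, b = 0.30:
- r = 0.5, null drug: (0.60 + 0.20)/(0.70 + 0.15) = 0.80/0.85 = 0.94
- r = 1.5, null drug: (0.60 + 0.60)/(0.70 + 0.45) = 1.20/1.15 = 1.04
- r = 0.5, true 0.80: (0.48 + 0.20)/0.85 = 0.68/0.85 = 0.80

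The same formula over other assumed shares gives, as null drug / true 0.80:

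| a v b | r = 0.5 | r = 0.7 | r = 1 | r = 1.5 |
|---|---|---|---|---|
| 30% v 30% | 1.00 / 0.84 | 1.00 / 0.85 | 1.00 / 0.86 | 1.00 / 0.88 |
| 40% v 30% | 0.94 / 0.80 | 0.97 / 0.84 | 1.00 / 0.88 | 1.04 / 0.94 |
| 30% v 40% | 1.06 / 0.89 | 1.03 / 0.88 | 1.00 / 0.86 | 0.96 / 0.84 |
| 50% v 30% | 0.88 / 0.76 | 0.93 / 0.82 | 1.00 / 0.90 | 1.09 / 1.00 |
| 10% v 30% | 1.12 / 0.91 | 1.07 / 0.87 | 1.00 / 0.82 | 0.91 / 0.76 |

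With equal shares, or with r = 1, a true 0.80 is attenuated, as the protocol says. Away from those cases a null drug can read either side of 1, and a true 0.80 is usually attenuated but can be exaggerated.

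**When a true protective effect is exaggerated.** The observed HR falls below θ when a(r − θ) < bθ(r − 1). For θ = 0.80:
- r = 0.5: a must exceed 0.4/0.3 = 1.33 times b
- r = 0.7: a must exceed 0.24/0.10 = 2.4 times b
- r = 1.5: a must be below 0.4/0.7 = 0.57 times b
- r between 0.80 and 1: no choice of shares exaggerates

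**Can one common rule give unequal shares?** If the drug is truly stopped at the end of supply, the 60-day tail makes up 60/(d + 60) of a course of d days: 67% at 30 days, 40% at 90 and 25% at 180. Courses averaging 180 days on lansoprazole and 90 on the comparator would give a = 0.25 and b = 0.40. A null drug then reads 1.125/1.20 = 0.94 at r = 1.5. With the course lengths swapped it reads 1.20/1.125 = 1.07. These are upper-end shares, since some tail time will be covered by stockpiled drug.

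**The case against.** The protocol's wording is a tendency, and it concerns a true association. A reader might infer that it claims error can only shrink the effect, but it does not say that. Nor is equal error always required: if off-PPI TB risk equals on-PPI risk, unequal error still attenuates. For a true 0.80 most of the scenarios above attenuate or leave the estimate unchanged. Exaggeration needs an off-PPI rate well away from the on-PPI rate together with a sizeable gap in shares. All of this stands.

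Nothing in the protocol says that course length or adherence differs by drug. The classification rules are the same for both groups, PPI preference is attributed mainly to cost, and exposure is described as long in many patients, which lowers the tail share. This also stands, and it is why no size can be claimed. It does not supply the missing condition, because similar shares are neither assumed in the limitations paragraph nor checked in the analyses the protocol describes.

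Some planned work bears on the question. The separate unexposed category lets the off-PPI rate be estimated, although the rate long after stopping need not match the rate in the tail. The analysis censoring at cessation or switch limits later misclassification, but cessation is still defined as more than 60 uncovered days, so the tail remains. The other sensitivity analysis only lengthens the tail, from 60 to 90 days. The myocardial infarction control, reported as null, and the zoster control reassure in part, since off-PPI risk for those outcomes need not match that for TB.

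**Conclusion.** The concern holds as a missing condition. Error unrelated to TB is not enough to support the stated direction of bias. The off-drug share must also be similar for the two drugs, or off-PPI TB risk must equal on-PPI risk. The protocol's own reason for separating unexposed time leaves the second alternative uncertain, and the limitations paragraph does not carry that reason over.

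The size is unknown. Under the assumed 40% v 30%, a null drug reads 0.94 at r = 0.5 and 1.04 at r = 1.5. At the wider 50% v 30% it reads 0.88 and 1.09.

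A reader might infer that the reported protective association is an artefact of exposure error. The documents do not support that: they give no shares or rates, the direction is open, and unequal error could equally have hidden a real effect. The supportable conclusion is narrower: a protective estimate cannot be called conservative on the stated condition alone.

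**What to change.** 1. Restate the limitations sentence: underestimation is expected if exposure error is unrelated to TB and, in addition, the off-drug share of classified time is similar in both drug groups or off-PPI TB risk equals on-PPI risk. Do not describe a protective result as conservative unless this is shown to be reasonable.
2. Tabulate by drug the course length, the share of prescriptions with imputed duration, and the share of exposed time beyond the estimated end of supply. Show the estimated TB rate in unexposed time alongside. The table would also show whether the single pooled median matters; no stated difference between the drugs justifies changing it in advance.
3. Add a sensitivity analysis that shortens the tail (for example 0 and 30 days, as well as the planned 90), or that separates tail time from supplied time by days since the end of supply. Days since the last prescription would not serve: a patient on a longer prescription may still be supplied, and the longest intervals largely overlap the unexposed state.

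The cost is a sentence, a table and reruns on prescription data already in use, with a small loss of precision in the added analysis. It will not detect non-adherence within the supplied period, so that part of the condition remains an assumption to be stated.
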